**Macro vascular circulation by flow-mediated dilatation (FMD)**

The FMD will be assessed by ultra-sonography (echo tracking) of the brachial artery and is based on the ability of vascular endothelial cells to respond to changes in shear stress. FMD is estimated as the percentage increase in vessel diameter from baseline conditions to maximum vessel diameter during hyperemia.

**Micro vascular circulation by Ionthophoresis**

Small amounts of a ionic vaso-active drug will diffuse through the skin by an electric field. An endothelial dependent (acetylcholine) and an endothelial non-dependent (sodium nitroprusside) vaso-active drug will be used to perfuse the skin and changes in skin blood flow will be assessed by Laser Doppler monitoring/ imaging.

***6.1.2 Measurements of secondary study outcomes***

Blood samples will be taken from the left arm, which is opposite to the one used for measuring functional ED measures at baseline (-1.5h) and at 1, 2, 3, 5, 6 hours after the milkshake by using a venflon.

**PBMC gene expression profiles** will be determined by using whole genome NuGO Affymetrix microarrays at baseline (-1.5h) and 3 and 6 hours after receiving the challenge. Expression profiles of genes selected from the microarrays will be assessed at all other blood collection time points by quantitative real time PCR (Q-PCR)

**White blood cell activation markers** will be determined at baseline and after 3 and 6 hours by using flow cytometry analysis (coulter Epics XL.MCL flow cytometry by Beckman Coulter)

**Plasma cytokine profiles** will be tested by quantitative immunoassays at rules Based Medicine laboratories (Austin, TX) at all blood collection time points. The cytokine profile of a panel of 120 proteins including will be determined. For detail on the 120 proteins, see:

<http://www.rulesbasedmedicine.com/services_human_antigen.asp>.

**Known plasma markers of endothelial function such as** NO, NOx, prostacyclin, cyclic adenosine monophosphate, cyclic guanosine monophosphate, cytokines, endothelin, intercellular adhesion molecule-1, vascular cell adhesion molecule-1, von Willebrand factor, plasminogen activator inhibitor-1, or thrombomodulin, selectins, integrins, HDL functionality, HDL lipid mediators and extracellular phospholipase secretory phospholipase A2-IIA will be determined at baseline and after 3 and 6 hours. Markers that are changed at these time points will also be measured at all other blood collection time points by using quantitative immunoassays, ELISA and at rules Based Medicine laboratories (see above).

**6.1.3 *Measurements of tertiary (additional) study outcomes***

Plasma glucose, triacylglycerol (TAG), FFA and insulin concentrations will be determined at the biochemical laboratory in Velp. Outcomes of these parameters are known and provide information about the normal physiological response. These tertiary study outcomes will therefore be used as a control.

**6.2 Study procedures**

**6.2.1 Information meeting**

An information meeting will be organized 6 weeks prior of the study. In this meeting the investigators will explain the background, objectives and set up of the study. Also the possible risks and burdens will be explained and during this meeting there will be time for the potential participants to ask questions.

**6.2.2 Screening**

There will be a screening visit planned 4 weeks prior of the beginning of the study in order to recruit participants who fulfill all criteria. The following data will be collected:

- Written informed consent
- 3ml of blood for fasting blood glucose
- Fasting urinary glucose and protein concentrations
- Length and height
- Hb values
- Blood pressure values
- A general medical questionnaire will be filled in

**6.2.3 Preparations prior to the Intervention**

All participants will receive a diary 2 weeks prior to the study. In this diary, the participants can keep track of any signs of illness, any deviations from the protocol or any possible side effects. In addition, further details (e.g. logistical) of the experiment will be elucidated.

**6.2.4 Intervention**

Participants will be asked to check in 30 min prior to the first data collection point (T=-2h) in order to be sure that measurements are taken at a ‘resting’ state. Before the start of each study day, the Hb value of each participant will be determined by using a hemoglobin analyzer (HemoCue 201). Participants with a Hb value below 8.4 mmol/L will not be measured and are asked to make a new appointment. If Hb values are normal (e.g. above 8.4mmol/L), a venflon will be placed into the antecubital vein of the participant’s forearm by qualified and experienced personnel. Functional measurements will be performed at baseline (T= -1.5h) and 3 and 6 hours after the intervention. The total time required for the functional measurements is set at 1.5 hours in total and the protocol is as followed:

- 15 min prior to the measurements, participants are asked to lie down on the bed
- Blood pressure will be measured (required for some measures below)
- Macro vascular regional arterial stiffness will be assessed by tonometry
- Macro vascular local carotid arterial stiffness will be assessed by ultrasound
- Macro vascular blood circulation will be assessed by FMD/ ultrasound
- Micro vascular blood circulation will be assessed by iontophoresis

Blood will be collected at baseline (T=-1.5) and 1, 2, 3, 5, and 6 hours after the intervention. An overview of the data collection points on each study day is shown in table 2.

**Table 2:** *protocol on each study day. NB. Data will be collected for two participants each day. The second participant will receive the same protocol, only all time points are delayed by one and a half hour.*

| Intervention time, after overnight fasting (in hours (h)) | -1.5h | 0h | 1h | 2h | 3h | 5h | 6h |
| --- | --- | --- | --- | --- | --- | --- | --- |
|  | (7.30am) | (9.00am) | (10.00am) | (11.00am) | (12.00am) | (14.00am) | (15.00am) |
| Consumption of the test meal |  | X |  |  |  |  |  |
| **Primary measurements** |  |  |  |  |  |  |  |
| Macro vascular:  Arterial stiffness  by tonometry | X |  |  |  | X |  | X |
| by ultrasound | X |  |  |  | X |  | X |
| Flow mediated dilatation | X |  |  |  | X |  | X |
| Micro vascular:  Iothophoresis | X |  |  |  | X |  | X |
| **Secondary measurements** |  |  |  |  |  |  |  |
| Total blood sampling (ml) | 56 |  | 8 | 8 | 56 | 8 | 56 |
| PBMC gene expression |  |  |  |  |  |  |  |
| By microarray analysis | X |  |  |  | X |  | X |
| By Q-PCR | X |  | X | X | X | X | X |
| White blood cell activation | X |  |  |  | X |  | X |
| Cytokines and markers of ED | X |  | X | X | X | X | X |
| **Tertiary measurements** |  |  |  |  |  |  |  |
| Plasma Insulin/FFA/TAG/glucose | X |  | X | X | X | X | X |

A total volume of 192ml will be collected from each participant during each collection day. An elucidation of this volume is given in table 3.

***Table 3:*** *Elucidation of blood volumes (ml)* taken for the secondary measurements

|  | T=-1.5 | T=1 | T=2 | T=3 | T=5 | T=6 | Overall |
| --- | --- | --- | --- | --- | --- | --- | --- |
| PBMC gene expression profiles | 16 | 4 | 4 | 16 | 4 | 16 |  |
| White blood cell activation markers | 20 | - | - | 20 | - | 20 |  |
| Cytokine and other ED markers | 20 | 4 | 4 | 20 | 4 | 20 |  |
| Total | 56 | 8 | 8 | 56 | 8 | 56 | 192 |

The participants will spend the entire day (approximately 9 hours) in the research room, where they will be able to read books, watch television/DVD, or relax in comfortable chairs. During the whole experiment , at least 2 persons other than the participants are in the room. At the end of the study day the participants will be offered a warm meal . At the end of the study, diaries will be collected.

A total of two participants will be evaluated on a single testing day. Person A will start at 7.00h and will finish at 16.30h. Person B will start at 8.30h and will finish at 18.00h. An overview of a single testing day in which two participants will be evaluated is given in table 4.

**Table 4:** *Time scheme during a study day. Two participants will be measured each study day. Person A will start at 7.00h and will finish at 16.30h. Person B will start at 8.30h and will finish at 18.00h. Time points in which blood will be collected are marked with a *.*

| **Time** | **T** | **Person A** | **Person B** | **T** | **Time** |
| --- | --- | --- | --- | --- | --- |
| **7.00** | -2 | arrival subject |  |  | **7.00** |
| 7.15 |  |  |  |  | 7.15 |
| 7.30 | -1.5 * | Functional |  |  | 7.30 |
| 7.45 |  | measurements |  |  | 7.45 |
| **8.00** | -1 | baseline |  |  | **8.00** |
| 8.15 |  |  |  |  | 8.15 |
| 8.30 |  |  | arrival subject | -2 | 8.30 |
| 8.45 |  |  |  |  | 8.45 |
| **9.00** | 0 | **Challenge** | Functional | -1.5* | **9.00** |
| 9.15 |  |  | measurements |  | 9.15 |
| 9.30 |  |  | baseline | -1 | 9.30 |
| 9.45 |  |  |  |  | 9.45 |
| **10.00** | 1* |  |  |  | **10.00** |
| 10.15 |  |  |  |  | 10.15 |
| 10.30 |  |  | **Challenge** | 0 | 10.30 |
| 10.45 |  |  |  |  | 10.45 |
| **11.00** | 2* |  |  |  | **11.00** |
| 11.15 |  |  |  |  | 11.15 |
| 11.30 |  |  |  | 1* | 11.30 |
| 11.45 |  |  |  |  | 11.45 |
| **12.00** | 3* | Functional |  |  | **12.00** |
| 12.15 |  | measurements |  |  | 12.15 |
| 12.30 |  | T=3 |  | 2* | 12.30 |
| 12.45 |  |  |  |  | 12.45 |
| **13.00** | 4 |  |  |  | **13.00** |
| 13.15 |  |  |  |  | 13.15 |
| 13.30 |  |  | Functional | 3* | 13.30 |
| 13.45 |  |  | measurements |  | 13.45 |
| **14.00** | 5* |  | T=3 |  | **14.00** |
| 14.15 |  |  |  |  | 14.15 |
| 14.30 |  |  |  | 4 | 14.30 |
| 14.45 |  |  |  |  | 14.45 |
| **15.00** | 6* | Functional |  |  | **15.00** |
| 15.15 |  | measurements |  |  | 15.15 |
| 15.30 |  | T=6 |  | 5* | 15.30 |
| 15.45 |  |  |  |  | 15.45 |
| **16.00** | 7 |  |  |  | **16.00** |
| 16.15 |  |  |  |  | 16.15 |
| 16.30 |  |  | Functional | 6* | 16.30 |
| 16.45 |  |  | measurements |  | 16.45 |
| **17.00** |  |  | T=6 |  | **17.00** |
| 17.15 |  |  |  |  | 17.15 |
| 17.30 |  |  |  | 7 | 17.30 |
| 17.45 |  |  |  |  | 17.45 |

**6.3 Withdrawal of individual participants**

Participants can leave the study at any time for any reason if they wish to do so without any consequences. The investigators can decide to withdraw a participant from the study for urgent medical reasons. After withdrawal of a participant, they will be replaced if this is still compatible with the study guidelines

**6.4 Follow-up of participants after withdrawal**

After possible withdrawal, no follow-up of participants will take place. In case of withdrawal due to medical complications, participants will be referred to a general physician.

**6.5 Premature termination of the study**

The procedures for premature termination of the study can be found in the adverse events protocol of the division Human Nutrition of Wageningen University.

**7. SAFETY REPORTING**

**7.1 Section 10 WMO event**

When it appears that the disadvantages of participation may be significant greater than was foreseen in the research protocol, participants and the reviewing accredited METC will be informed according to section 10, subsection 1, of the WMO.

**7.2 Adverse and serious adverse events**

Adverse events (AE) include any undesirable experience occurring to a participant during a clinical trial, whether or not considered related to the investigation. All AE reported by the participant or observed by the investigators will be recorded.

A serious adverse event (SAE) is any untoward medical occurrence or effect that at any dose results in death:

- Is life threatening (at the time of the event)
- Requires hospitalization or prolongation of hospitalization.
- Results in persistent or significant disabilities or incapacity
- Is a congenital anomaly
- Is a new event of the trial likely to affect the safety of the participants, such as an unexpected outcome of an adverse reaction, lack of efficacy of an IMP used for the treatment of a life threatening disease, major safety finding from a newly completed animal study, etc.

All SAE will be reported to the accredited METC that approved the protocol, according to the requirements of that METC.

**7.3 Follow-up of adverse events**

All AE will be followed until they have abated, or a stable situation has been reached. Depending on the event, follow-up may require additional test or medical procedures as indicated, and/or referral to the general physician or a medical specialist.

**8. STATISTICAL ANALYSIS**

To observe an effect of HF on EF, changes in primary outcome variables will be tested using repeated measures ANOVA (mixed model) using pre-defined contrasts, i.e. 3 versus 0 hrs and 6 versus 3 hrs. ANOVA will also be used to quantify the within- and between subject variation of the various measurements.

Changes in secondary outcome variables will be tested using repeated measures ANOVA (mixed model) using pre-defined contrasts, i.e. 3 versus 0 hrs and 6 versus 3 hrs. Additionally, incremental areas under the curve will be calculated for all significant altered secondary outcome variables using the trapezoïdal rule and compared between meals using one-way ANOVA. All statistical analysis will be performed with SPSS version 15.0.

Data analysis of the microarrays will be performed using a Bayesian linear regression model (implemented in the software package LIMMA; [www.bioconductor.org](http://www.bioconductor.org/)). Raw microarray data will be normalized using RMA quantile normalization. Statistically significant changed genes will be identified by student paired t-test followed by a false discovery rate correction (FDR) The latter is used to correct for multiple testing.

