**1.2 Functional measures of endothelial function**

EF can be assessed by several methodologies/functional measurements of which each has its own advantages and drawbacks. Currently, HF meal induced ED is only studied on a macro vascular level by using FMD. Flow mediated dilatation is a commonly used technique to investigate the ability of vascular endothelial cells to respond to changes in shear stress. However, this technique is time consuming and large variations in reproducibility are found in the literature (reviewed by De Roos *et al*. 2003 11).

There are other methodologies to monitor EF besides FMD, although these are not applied to monitor HF meal induced ED. Another way to (indirectly) indicate EF on macro vascular level is by measuring the arterial stiffness12. Arterial stiffness (i.e. impairment of the cushioning capacity) leads to an increase in systolic blood pressure and can be estimated by quantifying pulse pressure, but is better described by distensibility and compliance coefficients, pulse wave velocity and wave reflection. It is also possible to monitor EF on a micro vascular level. Abahji *et al.* (2006)13 observed impaired micro vascular EF after acute hyperhomocysteinemia by using ionthophoresis techniques. The question remains if these other methodologies are also applicable to observe a HF meal induced ED.

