**4.4 Sample size calculation**

Based on the methodological paper by de Roos *et al. (2003) 11*we can estimate that we need 7 subjects to obtain a 6 FMD% difference before and after the fat load with 90% power and alpha of 5%, using an within-subjects SD of 2.8 FMD%. Van Oostrom *et al.*(2003) observed a reduction from 13 FMD% to 3 FMD% after a high-fat load in healthy men 4. However, we know that the within-subject coefficient of variation for FMD can be large and that FMD measures differ between studies. 13 The latter may be due to methodological reasons18. Hence we propose to include 20 subjects, which enables us to detect a difference in 3 units of endothelial function as measured with ionthophoresis (paired t-test, SD 4.5 units, power 80%, alpha 5%), which seems plausible 13.

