**6. METHODS**

**6.1 Study outcomes**

***6.1.1 Measurements of primary study outcomes***

Four different non invasive functional measurements will be used to establish a reliable method to measure HF induced ED and to observe the effect of a HF meal on systemic arterial stiffness, local arterial stiffness, macro circulation and micro circulation. The total protocol of the EF measurements will take 1.5 hours (for details see paragraph 6.2.4). Functional measurements will be performed at baseline (T=-1.5) and 3 and 6 hours after the challenge, because previous studies observed a maximal response in macro vascular circulation by FMD after 3 hours that returned to normal after 6 hours4, 9. All functional measurements will be performed on the right side of the body in a climate controlled room.

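### Section 8 never compares the 6 h value with baseline, so a gradually building effect is tested weakly and persistence at 6 h has no direct test

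*Protocol*

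**What the plan says.** Section 8 names the same two time contrasts for primary and for secondary outcomes: "pre-defined contrasts, i.e. 3 versus 0 hrs and 6 versus 3 hrs". They are called pre-defined and introduced by *i.e.*, so the list reads as complete. No comparison of 6 h with baseline appears anywhere in the protocol. For secondary outcomes only, "incremental areas under the curve will be calculated for all significant altered secondary outcome variables using the trapezoïdal rule", and these areas are compared between meals.

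Section 6.1.1 sets the schedule: "Functional measurements will be performed at baseline (T=-1.5) and 3 and 6 hours after the challenge". The reason given is that "previous studies observed a maximal response in macro vascular circulation by FMD after 3 hours that returned to normal after 6 hours". The Summary defines the primary outcomes as vascular function before the high-fat meal and at both later times. On the methods other than FMD, Section 1.2 says "although these are not applied to monitor HF meal induced ED".

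**The concern.** The 6 h session is justified by a return to normal, which is a statement about 6 h relative to baseline. The contrast 6 versus 3 h asks something else: whether values moved after 3 h. It gives movement since 3 h, not distance from the starting point. One of the two post-meal values in the primary outcome is thus never compared with the pre-meal value.

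The pair of contrasts suits a curve that dips at 3 h and recovers by 6 h. That curve is taken from FMD. For arterial stiffness and skin microcirculation the protocol offers no time course after a high-fat meal, and its first research question asks which method is best suited to detect the effect. A method whose response builds more slowly than FMD would have its change divided between two contrasts and could look insensitive because of how it was tested.

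There may be a knock-on effect for secondary outcomes. Section 6.1.2 assays plasma markers at the remaining time points only if they changed at the main ones, and Section 8 computes areas only for significantly altered variables. If the two contrasts decide this, a slowly changing marker missed by both would receive neither.

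**Working it through.** **Inputs.** From Section 4.4: "Hence we propose to include 20 subjects"; a difference of 3 iontophoresis units; SD 4.5; power 80%; alpha 5%; paired t-test. From Section 8: the two contrasts. The 0 h of Section 8 is read as the baseline at T = -1.5 h, because no functional measurement is scheduled at 0 h.

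**Assumptions.** The SD of 4.5 is that of a paired difference and is the same for every pair of time points; errors are equally correlated over time; the tests are two-sided; one study day per meal is used; there is no multiplicity adjustment.

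**Step 1, the plan's own figure.** Paired t-test power uses the noncentral t distribution with n - 1 degrees of freedom and noncentrality (difference / SD) × √n. For 3 units: (3 / 4.5) × √20 = 2.98, critical value 2.093 on 19 df, power 0.807. The smallest n reaching 80% is 20, so the stated sample size reproduces.

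**Step 2, an effect split over two intervals.** Suppose the change from baseline is 1.5 units at 3 h and 3 units at 6 h. Each planned contrast then sees 1.5 units: (1.5 / 4.5) × √20 = 1.49, power 0.294. The contrast 6 h versus baseline sees the full 3 units, power 0.807.

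**Step 3, other time courses.** Single-contrast powers are from the formula above. The *at least one* columns come from simulating three time points under the stated assumptions, each contrast tested by a paired t-test.

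| Change from baseline at 3 h, 6 h | 3 v 0 | 6 v 3 | At least one planned | 6 v 0 | At least one of all three |
|---|---|---|---|---|---|
| Starts after 3 h (0, -3) | 5% | 81% | 82% | 81% | 92% |
| Gradual (-1.5, -3) | 29% | 29% | 55% | 81% | 84% |
| Sustained (-3, -3) | 81% | 5% | 82% | 81% | 92% |
| Half recovery (-3, -1.5) | 81% | 29% | 82% | 29% | 84% |
| Full return (-3, 0) | 81% | 81% | 92% | 5% | 92% |

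The clear loss of power is in the gradual row. In the sustained row the effect is found at 3 h, but nothing planned tests whether it is still there at 6 h.

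**Step 4, sensitivity to the triplicates.** Section 3.1 gives each meal three times. If all of the variance behind the 4.5 averages out over three days, the SD becomes 4.5 / √3 = 2.60. For the gradual pattern, power is then 69% per planned contrast and 95% for at least one, against more than 99% for 6 h versus baseline. If only half of the variance averages out, the SD is 4.5 × √(1/2 + 1/6) = 3.67 and per-contrast power is 41%. The per-contrast figure therefore runs from 29% to 69%, and the ordering does not change.

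**Step 5, precision of the missing comparison.** The 95% confidence interval for 6 h versus baseline has half-width 2.093 × 4.5 / √20 = 2.1 units.

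**Step 6, cost in false positives.** With no true effect, at least one of the two planned contrasts is significant in about 9% of simulated trials. With the third added, unadjusted, this becomes about 12.4%.

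**The case against.** The strongest defence is that the planned pair is sensible for the only time course the protocol cites. Under a 3-unit dip at 3 h with full return by 6 h, 6 versus 3 h has 81% power and 6 h versus baseline has 5%. The two contrasts then test impairment followed by recovery. The 6 h versus baseline difference is also their sum, so the same mixed model yields it from the same data, and an analysis plan not shown could list it. Return to normal explains the timing in Section 6.1.1; it is not among the research questions or hypotheses of Section 2.1. The gradual pattern is a scenario that the protocol neither describes nor supports with data, and 29% ignores the triplicates.

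Much of this stands. It limits the point to pre-specification and means that 6 versus 3 h should be kept. It does not remove the gap. The contrasts are listed as complete, so a later 6 h versus baseline test would be chosen after the fact, and the cited time course covers FMD only.

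A reader might infer several stronger things that the documents do not support:

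- *That a delayed effect cannot be detected.* An effect starting after 3 h is what 6 versus 3 h tests, with 81% power.
- *That a sustained effect is missed.* A 3-unit drop at 3 h is caught by 3 versus 0 h with 81% power; only its persistence goes untested.
- *That a partial rebound will be reported as full recovery.* Nothing in the protocol says a significant 6 versus 3 h result will be read that way.
- *That the shared 3 h value makes the planned pair unsound.* Under equal independent errors the planned contrasts correlate at -0.5, but 3 versus 0 h and 6 versus 0 h share the baseline and correlate at +0.5. Both members of either pair are falsely significant in about 1% of trials.

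**Conclusion.** The point holds as a gap in the pre-defined contrasts, of minor to moderate weight. The 6 h value is never compared with baseline for any primary or secondary outcome. For an effect that builds steadily to 3 units at 6 h, this means 29% power per planned contrast and 55% for at least one, where a direct comparison would have 81%. Persistence or completeness of recovery at 6 h has no direct test.

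These figures rest on 20 subjects, an SD of 4.5 for every pairwise time difference, a two-sided 5% level and one study day per meal. They improve to the extent that the triplicates reduce the SD, which the protocol does not allow one to determine. Effects fully present at 3 h, or arising wholly after 3 h, are tested as planned.

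Adding the comparison would not by itself establish return to normal. A non-significant difference is not equivalence, and the protocol states no margin. With a half-width of about 2.1 units, an estimate of zero would exclude a residual effect of 3 units but not one of 1.5.

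**What to change.** In Section 8, add 6 h versus baseline to the pre-defined contrasts for primary and secondary outcomes, and keep 3 versus 0 h and 6 versus 3 h. Report the new estimate with its 95% confidence interval, and state that non-significance will not be read as a return to normal.

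Replacing 6 versus 3 h is not advisable. Under the full-return pattern, the chance that at least one of two contrasts is significant would fall from 92% to about 82%, and the test of recovery itself would be lost.

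The change takes one line and needs no new data, visits or subjects. Its cost is one more contrast per outcome, which raises the chance of any false positive from about 9% to between 12% and 13% if unadjusted. It requires no change in how the control meal is used; Section 3.1 says the two meals will not be directly compared, and that is a separate matter.

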**2. OBJECTIVES**

The objectives are formulated to investigate the effect of a HF meal on EF. The primary objectives are to evaluate the effect of a HF meal on several measures of macro- and micro vascular EF. Our secondary objectives are to obtain more knowledge on the underling mechanisms of HF meal-induced ED and to identify early biomarkers of ED.

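### Panel proteins that change at 1 to 2 h and are back near baseline by 3 h are measured but have no planned test

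*Protocol*

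**What the plan says.** The secondary objectives (Section 2) are to learn more about mechanisms and "to identify early biomarkers of ED". Section 6.1.2 has blood drawn "at baseline (-1.5h) and at 1, 2, 3, 5, 6 hours after the milkshake by using a venflon". What is done with those samples differs by type of marker:

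- The 120-protein panel is assayed at all six times, without condition.
- Known plasma markers of endothelial function are assayed at baseline, 3 h and 6 h, and then "Markers that are changed at these time points will also be measured at all other blood collection time points".
- Gene expression is screened by "whole genome NuGO Affymetrix microarrays at baseline (-1.5h) and 3 and 6 hours after receiving the challenge"; only genes selected from the arrays go on to Q-PCR at the other times.
- White blood cell activation markers are assayed at baseline, 3 h and 6 h only.

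Section 8 gives the analysis. Secondary outcomes are tested by repeated measures ANOVA with two contrasts, 3 h v 0 h and 6 h v 3 h. It then adds that "incremental areas under the curve will be calculated for all significant altered secondary outcome variables using the trapezoïdal rule and compared between meals". No blood is drawn at 0 h, so 0 h is taken here to mean the baseline sample at -1.5 h. False discovery rate control is stated for the microarrays only.

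On timing, Section 6.1.1 explains the choice of 3 h and 6 h for the functional measurements: "previous studies observed a maximal response in macro vascular circulation by FMD after 3 hours that returned to normal after 6 hours".

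**The concern.** For the panel, the 1 h and 2 h values enter no stated contrast. The one planned analysis that could use them, the incremental area, is open only to variables already found altered, and the stated tests of change look at 3 h and 6 h. Selection therefore rests on the time when FMD impairment is expected to be greatest and on a time after it. A protein that moves beforehand and has settled by 3 h is generated as data and then left without a test. Changes that come before the functional response are among the more informative ones for mechanism, and could matter for early biomarkers. The protocol names both the contrasts and the condition on the area, so this is fixed in its text and not simply left open for a later analysis plan.

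**Working it through.** **Inputs.** n = 20, difference 3 units, SD 4.5, paired t-test, 80% power, 5% two-sided (Section 4.4, iontophoresis). Each meal is given three times (Section 3.1). Blood times are as in Section 6.1.2 and contrasts as in Section 8. The protocol gives no effect size for any biomarker, so the marker profiles below are assumptions.

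**1. The plan's own figure.** Standardised effect d = 3/4.5 = 0.667; noncentrality = 0.667 × √20 = 2.98; df = 19. The noncentral t gives 80.7% power, and 20 is the smallest n that reaches 80%. The stated sample size reproduces.

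**2. One contrast, if that ratio were borrowed for a biomarker.** Power of 3 h v baseline by the share of the effect still present at 3 h:

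- all (d = 0.667): 80.7%
- half (d = 0.333): 29.4%
- a quarter (d = 0.167): 10.9%
- none (d = 0): 5.0%

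These figures ignore the second contrast and the three repeat days.

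**3. Both contrasts together.** 20,000 simulated trials per profile, n = 20, independent errors with SD 1 at each time after removing differences between men, peak of 1 SD at 1 h. A marker is selected if 3 h v baseline or 6 h v 3 h has p < 0.05. Each cell gives one high-fat day / the mean of three high-fat days.

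| Assumed change at 0, 1, 2, 3, 5, 6 h | Selected by the plan | Direct 1 h v baseline |
| --- | --- | --- |
| none | 9.0% / 9.2% | 5.1% / 5.0% |
| 0, 1, 0.5, 0, 0, 0 (back by 3 h) | 8.9% / 9.1% | 84.7% / 99.9% |
| 0, 1, 0.6, 0.25, 0, 0 (a quarter left) | 19.3% / 39.0% | 84.9% / >99.9% |
| 0, 1, 1, 0.5, 0.25, 0 (half left) | 47.9% / 87.6% | 84.9% / >99.9% |
| 0, 1, 1, 1, 1, 1 (sustained) | 86.1% / 99.9% | 85.2% / 99.9% |

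Two independent 5% tests would give 1 − 0.95² = 9.75%. The figure is nearer 9% because both contrasts use the 3 h value. Repeating the meal does not help a marker that is back by 3 h, since there is no effect left to average. The direct contrast is shown before any correction for multiplicity.

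**4. The area without the significance condition.** With baseline carried to 0 h, the trapezoidal weights at 0, 1, 2, 3, 5, 6 h are 0.5, 1, 1, 1.5, 1.5, 0.5. Subtracting 6 × baseline turns the first weight into −5.5. For the profile back by 3 h, the mean is 1 × 1 + 1 × 0.5 = 1.5 and the SD is √(30.25 + 1 + 1 + 2.25 + 2.25 + 0.25) = √37 = 6.08. So d = 1.5/6.08 = 0.247 and power is 18% on one day. With three days, d = 0.247 × √3 = 0.427 and power is 44%. This tests the net area within the high-fat meal against zero. It beats 9%, but falls well short of the direct contrast.

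**5. Cost in multiplicity.** Two contrasts on 120 proteins make 240 tests; four make 480. With no correction and no true change, 240 × 0.05 = 12 false positives are expected now, and 480 × 0.05 = 24 with four contrasts. At the strictest step of a false discovery rate procedure the threshold moves from 0.05/240 = 0.00021 to 0.05/480 = 0.00010. For a change of 1 SD on one day (d = 1/√2 = 0.707), power at those thresholds is 14% and 10%. Most of the loss from 85% comes from correcting at all; doubling the tests adds little. The threshold relaxes as more proteins move.

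**The case against.** The strongest objection is that early biomarker need not mean early in hours. The protocol does not define the term. Section 2.1 describes candidates as changes that correlate with the functional measurements, and those exist only at baseline, 3 h and 6 h. Section 1.1 speaks of the initial stage of vascular disease. On that reading, screening at 3 h and 6 h fits the aim. This stands in part: the text does not require an early biomarker to move before 3 h. But Section 1.3 mentions precursors of dysfunction and the lack of early biomarkers in one sentence, and Section 2 also seeks mechanisms, so changes before the peak matter on either reading.

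A reader might infer that the 1 h and 2 h samples can never show a marker that moves before the peak, or that only late markers are kept. The documents do not support this. A marker that rises early and is still altered at 3 h can pass, and its 1 h and 2 h values are then analysed and show the onset.

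A reader might also see Table 2 as contradicting Section 6.1.2, because it marks cytokines and endothelial markers at every time. That row combines an unconditional panel with conditionally assayed markers, so it is compatible with both.

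Finally, known markers and genes with the same short-lived profile are missed as well, because they are not assayed at 1 h and 2 h. Two-stage assaying is defensible there: Table 3 allots 4 ml to cytokines and other markers at 1, 2 and 5 h, against 20 ml at baseline, 3 h and 6 h, and an unconditional early assay of the full list is not shown to fit. Contrasts for exploratory outcomes can also be added in an analysis plan, and the panel data will exist regardless, so nothing is lost for good.

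**Conclusion.** The point holds in a limited form. For the 120-protein panel, a change confined to 1 to 2 h and gone by 3 h is selected only at the false-positive rate: 5% per contrast and about 9% over both. That result does not depend on the size of the early peak or on the number of repeat days. It assumes a full return to baseline by 3 h and no further change at 6 h.

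The figures for partial return, 19% to 39% with a quarter left and 48% to 88% with half left, rest on assumed profiles and should be read as illustration. Those obtained by borrowing the iontophoresis ratio (29% and 11%) are weaker still as guides.

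The primary outcomes are untouched. This is an inexpensive improvement to an exploratory screen that serves a stated secondary objective.

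**What to change.** In Section 8, for analytes measured at all six times:

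- Add 1 h v baseline and 2 h v baseline as pre-defined contrasts, or calculate the incremental area for every panel protein without first requiring significance. The contrasts are the sharper choice for a short-lived change, as the working shows.
- State a false discovery rate correction across all panel tests, covering the existing two contrasts as well as the new ones.

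Leave the two-stage assay of known markers and genes as it is.

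The cost is wording and analysis of data already planned. More tests enter the correction, so power per contrast falls slightly for each added set. Introducing a correction at all costs more than that, but the panel needs one even with the present two contrasts. No extra blood, assays or visits are required.
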